### Research aim

The purpose of this study is to test whether UBE-TLIF is non-inferior to MT-TLIF in treating patients with DLSS in terms of efficacy and safety.

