### Outcome measurements

#### Primary outcome

The main outcome of the study is the ODI score at 1-year postoperation, which is a 10-item questionnaire specific to low back pain patients, including pain intensity, personal care (washing, dressing etc), lifting, walking, sitting, standing, sleeping, sex life (if applicable), social life and travelling. Each of the 10 items is scored from 0 to 5. Total scores are calculated by dividing the actual by the maximum score of 50 and converting it to a percentage. The score of 100% is recognised as the highest score, signifying the greatest dysfunction severity.^19 20^

The minimal clinically important difference (MCID) is a threshold value that patients and clinicians perceive as clinically meaningful. The clinically acceptable MCID in reported ODI scores is 8–12. However, to date, there is no consensus on calculating the optimal MCID for the ODI scores in groups.^21^,^23^ Consequently, following discussion, we adopted 8 as the MCID within clinically acceptable range. By comparing the ODI score 1 year after surgery, we can determine whether UBE-TLIF is not inferior to MT-TLIF within the non-inferiority margin of 8.

Considering that the condition of most enrolled subjects will be stabilised at 1-year postoperation, the assessment time frame of 1-year ODI is between 12 and 15 months after the operation. In case subjects do not return to the hospital for follow-up on time during this period, a telephone follow-up will be conducted to complete the ODI questionnaire.

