### Statistical analysis

In this study, three analysis sets will be required. For the safety analysis set, any adverse event (AE) will be recorded from patients who have undergone UBE-TLIF or MT-TLIF following randomisation. In the full analysis set, all participants who were randomised to the surgical intervention and for whom complete data sets were accessible after randomisation. In instances of missing data, we employed the last observation carried forward and baseline observation carried forward methods for imputation. For the per-protocol cohort, at least 90% of subjects should fulfil the following criteria: (1) receive either UBE-TLIF or MT-TLIF treatments; (2) with no violation of the protocol; (3) complete the full follow-up and (4) obtain all required data. Continuous variables, including VAS score, ODI score, operation time, intraoperative blood loss, serum CK and CRP level, DH, LL, SF-36, QoL EQ-5D as well as hospital stay, will be expressed as means±SDs, while categorical data, including vertebral fusion rate, will be shown as frequencies. The independent t-test and Pearson χ^2^ will be applied to analyse continuous and categorical variables, respectively. If indicated, statistical analysis between subgroups will be performed. All statistical analyses will be performed using Statistical Product and Service Solutions (V.26.0, IBM) by the principal biostatistician. A p<0.05 (two sided) will be considered statistically significant.

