### Sample size

The MCID for ODI scores reported in similar studies is 8–12.^22 23^ After discussing among experienced professors from the spine surgery department, 8 in ODI score is chosen as the margin of non-inferiority (ðN) in this study. Based on the Consolidated Standards of Reporting Trials 2010 statement,^28^ it is assumed that the expected response is the same in both groups, the estimated true difference between the two surgeries is 0, and the ðN is 8. The SD is estimated to be 13 based on previous studies.^29^ The test level is one sided (α=0.025), and the test power (1−β) is 0.8. Considering that 10% of population may loss to follow-up, a total of 96 subjects are required in this clinical study.

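### The analysis section assigns the primary ODI a two-sided test of difference and does not carry the margin-8 non-inferiority rule for which the trial is sized

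*Protocol article*

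**What the plan says.** The Research aim section sets the question: "The purpose of this study is to test whether UBE-TLIF is non-inferior to MT-TLIF in treating patients with DLSS". It extends this to both efficacy and safety.

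The Primary outcome section fixes the endpoint ("The main outcome of the study is the ODI score at 1-year postoperation", where a higher score is worse). It says that by comparing these scores "we can determine whether UBE-TLIF is not inferior to MT-TLIF within the non-inferiority margin of 8". It names no test and no confidence-interval rule.

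The Sample size section states that "8 in ODI score is chosen as the margin of non-inferiority" and that "the estimated true difference between the two surgeries is 0". It takes an SD of 13, one-sided α of 0.025, power of 0.8 and 10% loss to follow-up, and arrives at 96 patients.

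The Statistical analysis section names ODI in one list with VAS, operation time, blood loss, laboratory values, radiological measures, quality of life and hospital stay. It assigns the independent t-test to continuous variables and Pearson χ² to categorical ones, of which fusion rate is the only one named. It ends with one rule for everything: "A p<0.05 (two sided) will be considered statistically significant". The margin of 8 does not appear in that section.

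**The concern.** A non-inferiority trial needs a rule that sets the estimated difference, with its uncertainty, against the margin. The analysis section gives the primary endpoint the same difference test as every secondary variable. A two-sided p-value against zero answers whether the arms differ. It does not answer whether UBE-TLIF is worse by less than 8 points.

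Two things are at stake. The stated power of 0.8 and one-sided error of 0.025 belong to a test that the analysis section does not describe. And a reader who has only a p-value against zero may be drawn to treat a non-significant result as evidence of non-inferiority, which would remove the protection that the margin is meant to give.

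A smaller, related point is that the Research aim claims non-inferiority in safety, while the only margin in the article is for ODI.

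**Working it through.** **Inputs.** Margin 8, SD 13, true difference 0, one-sided α 0.025, power 0.8 and 10% loss (Sample size section); 1:1 allocation (Study design and settings section).

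**1. Reproduce the sample size.**
- Normal approximation: n per arm = 2 × [13 × (1.960 + 0.842) / 8]² = 41.45, so 42. Then 42 / 0.9 = 46.7, so 47 per arm and 94 in total.
- Noncentral t: 42 per arm gives power 0.796 and 43 gives 0.805, so 43 are needed. Then 43 / 0.9 = 47.8, so 48 per arm and 96 in total.

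The figure of 96 is therefore reproduced, and it belongs to the one-sided 0.025 test against 8.

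**2. Precision with 43 evaluable per arm.**
- SE = 13 × √(2/43) = 2.80.
- The t quantile on 84 degrees of freedom is 1.989, so the 95% CI half-width is 1.989 × 2.80 = 5.58.
- At that SD, the margin test succeeds when the observed difference (UBE-TLIF minus MT-TLIF) is below 8 − 5.58 = 2.42.

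**3. The two rules when the arms are truly equal.**
- Difference test: p<0.05 in 5% of trials by construction, 2.5% of them in favour of UBE-TLIF.
- Margin test: succeeds in 80.5%.
- Discordance: the margin successes consist of the 2.5% significantly favouring UBE-TLIF and 80.5 − 2.5 = 78.0% that are non-significant. Non-significant trials make up 95%, so 95 − 78 = 17% give p≥0.05 while the CI still reaches 8 or more. A simulation of 400,000 runs gives the same 17%.

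**4. The consequence if a non-significant result were read as non-inferior.** This rule is hypothetical; the article does not state it. For a true difference of 8, the chance of p≥0.05 is one minus the power to detect 8 points:
- 43 per arm: 1 − 0.805 = 19.5%.
- 48 per arm: 1 − 0.847 = 15.3%.

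The margin test would pass such an arm in 2.5% of trials. For a true difference of 6 with 43 per arm, p≥0.05 occurs in 43.8% of trials, against 10.5% success for the margin test.

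**5. Can a significant disadvantage lie inside the margin?** The observed difference would have to exceed 5.58 and also be below 2.42, which is impossible at an observed SD of 13. It would need a half-width below 4, that is an observed SD below 4 / (1.989 × √(2/43)) = 9.3.

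**6. Alpha.** Requiring the upper limit of a two-sided 95% CI to lie below 8 is the same as a one-sided 0.025 test against 8. Sections that name two-sided 0.05 and one-sided 0.025 therefore do not disagree on the size of the error.

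**The case against.** The strongest reply is that the article already states the criterion. The Primary outcome section ties the 1-year ODI comparison to the margin, and the Sample size section repeats it. The null value of the t-test is not written down, a t-based comparison of means also yields the CI that is needed, and the closing p<0.05 sentence may be a general convention for a list of mostly secondary variables. The article is also a condensed document, and an analysis plan that is not shown may hold the formal rule.

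Much of this stands. The intent to use the margin is clear, and three stronger readings are not supported:
- A reader might infer that the alpha levels contradict each other. They do not (step 6).
- A reader might infer that the plan will declare non-inferiority from p>0.05, or failure from a small significant difference. No section says either. The Primary outcome section points the other way, and the second case cannot arise at the planned SD (step 5).
- A reader might infer that safety non-inferiority is to be shown by a χ² test. The analysis section never assigns that test to complications, and any statement about precision for a typical complication rate would need a rate that the article does not give.

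What does not stand is the defence by omission. The analysis section is not silent: it names ODI, fixes its test and fixes its significance rule, and none of these refers to the margin. A better rule in an analysis plan would still leave this text at odds with it.

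**Conclusion.** The point holds in a limited form. The analysis section does not state the test that the Primary outcome section intends and the Sample size section powers. The fault is in the hypothesis and decision rule, not in alpha, the margin or the sample size, which agree with one another.

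On the plan's own assumptions the two rules are far apart: about 5% against about 80% positive results when the arms are equal. The 19.5% and 15.3% figures measure the risk only under a misreading that the text leaves open but does not prescribe. All figures assume normally distributed scores with SD 13 and either 43 evaluable patients or the full 48 per arm. Taking zero as the null value of the t-test is the natural reading, but an inference.

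Because this concerns the trial's single primary conclusion, it should be settled before allocation is revealed; a rule written later would look chosen to suit the data. The safety wording is a secondary point: the aim of showing UBE-TLIF "non-inferior to MT-TLIF in treating patients with DLSS in terms of efficacy and safety" goes further than a margin defined for ODI alone can support.

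**What to change.** In the Statistical analysis section, add a rule for the primary endpoint: non-inferiority is concluded if the upper limit of the two-sided 95% CI for the difference in mean 1-year ODI (UBE-TLIF minus MT-TLIF) is below 8, which is equivalent to a one-sided test at 0.025 against the margin. State that two-sided p<0.05 applies to secondary comparisons only. If an analysis plan exists, use the same wording there.

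In the Research aim section, limit the non-inferiority claim to 1-year ODI, and say that complications will be reported as rates with 95% CIs.

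The cost is a few sentences. The sample size stays at 96, and no further data or patients are needed.

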### Sample size

The MCID for ODI scores reported in similar studies is 8–12.^22 23^ After discussing among experienced professors from the spine surgery department, 8 in ODI score is chosen as the margin of non-inferiority (ðN) in this study. Based on the Consolidated Standards of Reporting Trials 2010 statement,^28^ it is assumed that the expected response is the same in both groups, the estimated true difference between the two surgeries is 0, and the ðN is 8. The SD is estimated to be 13 based on previous studies.^29^ The test level is one sided (α=0.025), and the test power (1−β) is 0.8. Considering that 10% of population may loss to follow-up, a total of 96 subjects are required in this clinical study.

### AE and serious AE

Surgery-related AEs from both arms will be reported and documented throughout the study period.

Intraoperative complications include dural tear, nerve root injury, pedicle screw misplacement, endplate fracture, cardiopulmonary complications, allergic reactions and other unpredictable complications. Postoperative complications include cerebrospinal fluid leakage, neurological deficit or deterioration, excessive postoperative drainage volume (>400 mL/day), postoperative infection, surgery-related thrombotic events, pedicle screw breakage, cage subsidence or migration, cardiopulmonary complications, haematoma within the spinal canal and other unpredictable complications.^30^,^32^

During the intervention and follow-up periods of this trial, any AE will be identified promptly and managed properly.

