#### Secondary outcome

The secondary outcomes of this study will assess ODI score at additional time points, VAS, SF-36, EQ-5D, radiological indicator (DH, LL angles and vertebral fusion rate) and hospitalisation information. The data collection schedule is presented in table 2. For those who cannot come for follow-ups, our research assistant will contact them by phone or email to complete the questionnaire.

**Table 2 T2:** The time schedule for collection of data for this trial

	Day≤−1	Day1	Day2–29	Day30±7 days	Day90±7 days	Day180±7 days	Day360±7 days
Inclusion and exclusion criteria	**√**						
Signing of informed consent form	**√**						
Demographic assessment	**√**						
Physical examination	**√**						
Operation time/Intraoperative blood loss		**√**					
Serum CK/CRP			**√**				
Length of stay			**√**				
ODI score	**√**			**√**	**√**	**√**	**√**
VAS score	**√**			**√**	**√**	**√**	**√**
SF-36-PF	**√**			**√**	**√**	**√**	**√**
SF-36-BP	**√**			**√**	**√**	**√**	**√**
QoL EQ-5D	**√**			**√**	**√**	**√**	**√**
Disc height	**√**				**√**	**√**	**√**
Lumbar lordosis angles	√				√	√	√
Vertebral fusion rate							**√**
Complications		**√**	**√**	**√**	**√**	**√**	**√**
Adverse events		**√**	**√**	**√**	**√**	**√**	**√**

√, This refers to the data collection at the scheduled time.

BPbody painCKcreatine phosphokinaseCRPC reactive proteinEQ-5DEuroQol 5 DimensionsODIOswestry Disability IndexPFphysical functioningQoLquality of lifeSF-3636-Item Short Form SurveyVASVisual Analogue Scale

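### The protocol gives two rules for which adverse events are documented: any event, or surgery-related events

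*Protocol article*

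**What the plan says.** Four places in the protocol article bear on which adverse events reach the data.

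- **AE and serious AE, opening sentence:** "Surgery-related AEs from both arms will be reported and documented throughout the study period".
- **AE and serious AE, closing sentence:** during intervention and follow-up, "any AE will be identified promptly and managed properly". It does not say that these events are recorded.
- **Statistical analysis, safety analysis set:** "any adverse event (AE) will be recorded from patients who have undergone UBE-TLIF or MT-TLIF following randomisation".
- **Table 2 (under Secondary outcome):** a row headed "Adverse events", separate from the complications row. Both are ticked at Day 1, Day 2–29, Day 30, Day 90, Day 180 and Day 360, and neither is limited to surgery-related events.

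The AE section also lists complications. The postoperative list is open-ended and ends with "cardiopulmonary complications, haematoma within the spinal canal and other unpredictable complications".

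For patients who do not attend, the Primary outcome section says "a telephone follow-up will be conducted to complete the ODI questionnaire", and the Secondary outcome section says "our research assistant will contact them by phone or email to complete the questionnaire".

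The Research aim is non-inferiority in both efficacy and safety.

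**The concern.** Staff who follow the AE section and staff who follow the Statistical analysis section would complete the case report form differently for the same event. Under one rule every event is entered. Under the other, someone first decides whether the operation caused it, and an event judged unrelated need not be entered.

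The order matters. If all events are recorded and then classified, the classification can be reviewed and the analysis repeated with and without the unrelated events. If the classification comes first, the excluded events leave no record and cannot be recovered at analysis.

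Some listed items, such as cardiopulmonary events and the unpredictable remainder, leave room for opinion about cause. The Introduction itself says that drawbacks of UBE-TLIF may increase perioperative complications, so the comparison of event counts between arms is one the trial is expected to inform.

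**Working it through.** The plan gives no figure on this point to reproduce: no expected AE rate, no expected share of unrelated events and no safety margin. The sample size of 96 rests on the ODI and has no bearing here. The check is therefore a comparison of the texts, followed by the algebra of what a relatedness filter would do.

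**Step 1: the rules side by side**

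| Place | Events covered | What is done with them |
|---|---|---|
| Statistical analysis, safety set | any AE in operated patients | recorded |
| Table 2, adverse events row | no limit stated | collected at six time points, Day 1 to Day 360 |
| AE section, opening | surgery-related | reported and documented |
| AE section, closing | any AE | identified and managed |

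The first two rows agree with each other. The last two, read together, separate what is documented (surgery-related) from what is managed (any). That separation is incompatible with the first row. Nothing in the article says which rule takes precedence.

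**Step 2: who would apply the filter**

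The AE section names no assessor of relatedness. The Blinding section and the Discussion say that clinical assessment is done by clinicians unaware of group. The Data collection, management and monitoring section says that form filling is done by blinded research assistants. The strengths and limitations box and the Discussion say that the surgeons cannot be blinded. None of these assigns the relatedness judgement to anyone.

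**Step 3: what the filter would do to the counts**

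Let arm k have A_k adverse events, of which a share u_k is judged not surgery-related. The documented count is

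D_k = A_k × (1 − u_k).

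Then

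- ratio of documented counts: D_1/D_2 = (A_1/A_2) × (1 − u_1)/(1 − u_2);
- difference of documented counts: D_1 − D_2 = A_1(1 − u_1) − A_2(1 − u_2).

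If u_1 = u_2 = u, the ratio is unchanged and the difference shrinks by the factor (1 − u). If u_1 and u_2 differ, the ratio moves away from the true one, towards either arm.

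The article gives none of A_1, A_2, u_1 and u_2, so no size and no direction follow from it. The algebra shows only that the AE section's rule leaves the comparison open to distortion, while recording everything (u_1 = u_2 = 0 at the documentation stage) does not.

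**The case against.** The strongest reply is that this is loose wording in one sentence. The AE section does not say that *only* surgery-related events are documented. The safety set definition and Table 2 both point to full capture, the complication list is open-ended, and a data safety monitoring committee reviews efficacy and safety data for all patients. A condensed article may also leave the assessor of relatedness and the follow-up call script to the full protocol.

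Much of this stands, and it limits what can be claimed. It does not remove the contradiction, because the article itself states both rules. The committee can review only what has been documented.

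A reader might infer several stronger points that the document does not support:

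- **Unblinded surgeons decide relatedness.** The article says that surgeons cannot be blinded, but not that they make this judgement. It describes blinded assessors and form-filling staff.
- **Patients followed remotely are not asked about events and are counted as event-free.** The telephone and email sentences explain how questionnaires are completed. They do not say that events go unasked, Table 2 schedules events at those time points, and no rule is given for patients without an AE assessment.
- **Neurological deterioration goes unassessed.** Table 2 ticks "Physical examination" only before surgery. But the AE section counts neurological deficit or deterioration among the complications, and complications are scheduled at every later time point.
- **The safety counts are understated.** This would follow only if the AE section overrides the other two places, and nothing says that it does.

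**Conclusion.** The concern holds as an internal contradiction on the scope of AE capture. The Statistical analysis section and Table 2 cover any AE; the opening of the AE section covers surgery-related AEs, and its close promises only identification and management for the rest. On the assumption that the AE section governs, a relatedness judgement by an unnamed assessor precedes documentation, and by-arm safety counts may be filtered. No numerical size or direction can be attached to this.

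The primary ODI analysis is not affected. The point is still worth correcting because safety is part of the stated aim, an undocumented event is lost for good, and the remedy is cheap.

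**What to change.** Reword the AE and serious AE section to match the Statistical analysis section and Table 2:

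- all AEs are documented from Day 1 to the last contact and reported by arm for the safety analysis set;
- relatedness to surgery is recorded as a separate, secondary classification and is not a condition for entry;
- the classification is made, where possible, by the clinicians already blinded to group.

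As a low-cost addition, state in the Primary outcome and Secondary outcome sections that a telephone or email contact also collects the complication and AE items that Table 2 already schedules at that time point. This makes explicit what the schedule implies.

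The cost is wording in the protocol and, where needed, the case report form, plus a few questions in contacts already planned. The downside is that more unrelated events will be listed and reported AE rates will rise somewhat in both arms. The separate relatedness classification lets readers see both counts.

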## Discussion

The current protocol describes the rationale, non-inferiority design and methods of this randomised, controlled clinical trial that compares the efficacy and safety of UBE-TLIF to MT-TLIF in patients of DLSS. The non-inferiority design can not only demonstrate the efficacy of UBE-TLIF compared with MT-TLIF but also focus on exploring the advantages beyond efficacy. Furthermore, it can avoid ethical concerns and has more ethical value than placebo-controlled or no-treatment-controlled clinical trials.^33^ Moreover, to avoid potential bias, all surgeries are performed by surgeons who have 10-year operation experience and are familiar with the two surgical procedures.

Moreover, the primary outcome in this study is the ODI score at 1-year postoperation. MCID was used to determine the sample size of this trial, which may facilitate the final analysis. Additionally, a majority of the outcomes in this study are self-reported by the subjects, including the VAS score, ODI score, SF-36 questionnaire and EQ-5D questionnaire, which will help minimise observation bias to some extent.

However, there are still some potential limitations that need to be addressed. The surgeon cannot be blinded for the study because the protocols for the two surgeries are different. However, to reduce bias as much as possible, investigators who are blinded in the group assignment process will perform the clinical assessment, including baseline evaluation. Additionally, all data will be collected from a single institution with a relatively small patient number. Larger multicentre studies are needed to confirm the efficacy and safety of MT-TLIF and UBE-TLIF in treating DLSS in future.

In conclusion, this study aims to compare the efficacy and safety of MT-TLIF and UBE-TLIF in treating patients with DLSS. The completion of this study will not only examine the use of UBE-TLIF in lumbar spinal stenosis but also provide helpful clinical references.

